### Eligibility criteria {10}

#### Inclusion and exclusion criteria

Participants must be aged between 12 and 18 years and be in the 6th to 12th grade. We chose this age group for two reasons: (1) The onset of adolescence brings about a clear increase in social, cognitive, and emotional challenges and expectations. Furthermore, neurological and cognitive change processes are underway [60]. Taken together, this can correspondingly increase self-perceived stress. (2) Epidemiological data show that the end of childhood, the beginning of adolescence, and adolescence itself represent the period with the highest risk of onset of mental disorders [28, 61].

Only one exclusion criterion will be applied: lack of informed consent from the adolescents or their parents/guardians. Moreover, we will assess the presence of a psychiatric illness with accompanying psychotherapy in order to exclude these students from data analysis.

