## Trial design {8}

The *LessStress* trial is designed as a cluster-randomised, controlled, non-blinded superiority trial with two parallel groups and a primary endpoint of self-perceived stress after 6 months. We will perform a random assignment on the school level with a 1:1 allocation ratio. The study will last for 6 months and will include four measurement time points: Pre = baseline, Post = student and teacher evaluation, T2 = 3-month follow-up, and T3 = 6-month follow-up (Fig. 1).

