### Provisions for post-trial care {30}

One positive side effect of this trial is the networking between schools and clinicians. We aim to reduce stigmatisation and encourage communication. If any student requires healthcare during or after the study, the Department of Child and Adolescent Psychiatry of Rostock will offer appointments. We are confident that by being present and talking to the schools and students, we can lower the threshold, enabling students to seek help more frequently and faster.

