### Plans to promote participant retention and complete follow-up {18b}

To promote retention throughout the study and maximise the completeness of data collection, we will give monthly feedback to the school heads, the involved teachers, and the participating students. Feedback may consist of a little insight into results of the first data collection, schedule reminders, a newsletter, or small business gifts (pens or stickers).

Should any student withdraw from the study for any reason, he or she must inform us, whether we are permitted to use the data already collected or we should delete it. If deletion is requested, the student must provide us with his/her pseudonym to enable deletion.

If non-retention occurs and more than one follow-up data assessment is missing for a student, this student will not be included in the analysis.

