### Methods for additional analyses (e.g. subgroup analyses) {20b}

We plan to split all of the participant data into subgroups for comparisons between males and females, different school types, age categories (younger vs. older determined by school grade), and healthy vs. clinically relevant. Depending on the variables, different methods will be used (*t*-test, Wilcoxon test, chi-squared), but we prefer multilevel modelling to explore associations between intervention effects and student characteristics.

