### Methods in analysis to handle protocol non-adherence and any statistical methods to handle missing data {20c}

If parts of the protocol need to be changed, this will always occur in consultation with the study management and the cooperation partners. The final decision on any changes will be made by the study management. Missing data should be minimised by the online survey. However, if this should occur, the procedure of multiple imputation will be chosen.

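### Two rules drop consenting students of already randomised schools from the analysis (psychotherapy, with no time point fixed; both follow-ups missing), using information gathered after allocation is known

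*Protocol article*

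**What the plan says.** All references are to the protocol article.

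- **Inclusion and exclusion criteria.** "Only one exclusion criterion will be applied: lack of informed consent from the adolescents or their parents/guardians". The text then adds a removal at the analysis stage: "we will assess the presence of a psychiatric illness with accompanying psychotherapy in order to exclude these students from data analysis". No time point or source for this status is given. Data collection is by student questionnaire throughout, so self-report is the likely source, but that is an inference.
- **Retention {18b}.** If "more than one follow-up data assessment is missing for a student, this student will not be included in the analysis".
- **Missing data {20c}.** For missing data, "if this should occur, the procedure of multiple imputation will be chosen", with no stated limit on who is imputed.
- **Trial design {8}.** Schools are randomised 1:1. After baseline and a post-lesson evaluation there are two follow-ups: "T2 = 3-month follow-up, and T3 = 6-month follow-up".
- **Timing and openness.** Schools learn their arm at once by mail (Concealment mechanism). Participants know their group (Procedure for unblinding). The first assessment falls 14–30 days after randomisation (Participant timeline).

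The article names no analysis set that would override either removal.

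**The concern.** The comparison between arms is protected by randomising schools and analysing their students as allocated. Each of these rules instead lets something learned after allocation decide who is counted. If being in therapy, or having no follow-up at all, is related both to arm and to how stress develops, the students who remain are no longer comparable between arms.

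The therapy rule is the more serious, because as written it permits exclusion on a status first reported at T2 or T3. It also sits awkwardly with the Discussion, which describes universal prevention as aimed at a large, unselected population. A primary result that leaves out students in treatment answers a narrower question than the one the programme is meant to serve.

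**Working it through.** **1. Order of events.** Randomisation comes first, then immediate notice to schools, then baseline 14–30 days after randomisation, then the lesson within 21 days of baseline, then T2 and T3. Therapy status can be recorded at baseline at the earliest, and missing follow-ups are known only later. Both rules therefore act on information collected after disclosure of the arm, even on the most favourable reading of the therapy rule.

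**2. What the follow-up rule removes.** There are two follow-ups, so more than one missing means 2 of 2. The primary outcome is the PSS-10 at 3 and 6 months (Outcomes {12}). The rule therefore removes exactly the students with no primary outcome value. A student with either T2 or T3 stays in.

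**3. Whether the arm could affect therapy status.** Before T3, intervention staff are trained, including role-plays on disclosed self-harm and acute distress (Adherence). Their students have the lesson and the booklet (Intervention). Waiting-list schools are offered the programme only after the 6-month assessment (Explanation for the choice of comparators). Exposure between baseline and T3 thus differs by arm in ways that could plausibly change who enters therapy or says so. The article does not show that it does.

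**4. Form of the bias.** Statistical methods {20a} compares the arms on change. For arm *a*, let p_a be the share excluded, and let g_a be the mean change of the excluded students minus the mean change of all consenting students in that arm.

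- Mean change of those kept = true mean change − p_a·g_a/(1 − p_a)
- Shift in the intervention-minus-control contrast = p_W·g_W/(1 − p_W) − p_I·g_I/(1 − p_I)

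If p and g are the same in both arms, the two terms cancel and the shift is 0. If the excluded students change as the others do (g = 0 in both arms), the shift is also 0 whatever the exclusion rates. Otherwise it can take either sign. The article gives none of p_I, p_W, g_I and g_W, so neither size nor direction follows from it.

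**5. The only budget for loss.** Sample size {14} reproduces from its own base figure:

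- Clustering effect: 1 + (80 − 1) × 0.05 = 4.95
- 306 × 4.95 = 1514.7, rounded up to 1515
- 25% of 1515 = 378.75, rounded up to 379
- 1515 + 379 = 1894

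The 25% is attributed to moving away, sickness or other causes. Therapy exclusions are not named, and the open-ended last category leaves unclear whether they are covered.

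**The case against.** The best defence of the therapy rule is that it stands under eligibility, where a status taken at entry is the natural reading, and that a condensed article may leave the exact time point to the full protocol. Leaving already treated students out of a prevention analysis is a legitimate target population if their status is fixed at baseline. The two eligibility sentences can also be read together: the first governs taking part, the second governs the analysis. This softens the conflict with the single exclusion criterion. It does not remove the exclusion after allocation, and the text as it stands does not tie the rule to baseline.

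Several stronger readings are tempting and are not supported:

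- **That the deletion rule contradicts multiple imputation.** Imputation can still serve students missing one follow-up or single items, so the two can coexist. Retention {18b} and Missing data {20c} should nevertheless be reconciled.
- **That the result is a completer analysis.** Students with one follow-up are kept.
- **That the article itself predicts an arm effect on help-seeking.** The hope of "enabling students to seek help more frequently and faster" is tied to the trial's presence in schools generally and does not separate the arms.
- **That the "healthy vs. clinically relevant" subgroup is emptied.** Clinical relevance is not defined by therapy, the PHQ-4 has its own severity bands, and symptomatic students without therapy remain.
- **That the bias can be given a number.** Suppose, purely by assumption, that 5% are excluded in one arm and 10% in the other, and that they score 1 SD higher. The follow-up means then shift apart by 0.10/0.90 − 0.05/0.95 = 0.111 − 0.053 = 0.058 SD, or 29% of d = 0.2. That is a shift in level. If the same gap exists at baseline, it cancels in a comparison of change. The rates and the gap have no source in the article.

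**Conclusion.** The point holds in a limited form. Two stated rules select students on information gathered after allocation is known, in an open trial, and nothing in the article overrides them. The therapy rule carries the greater risk because its time point is open and because it narrows a universal programme to students not in treatment. The follow-up rule carries less, since the students it removes have no primary outcome value, but it still departs from the arms as allocated and discards their baseline data.

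No magnitude can be stated. A bias requires the excluded share, or the excluded students' change relative to their arm, to differ between arms, and the article neither shows this nor rules it out. If the full protocol fixes therapy status at baseline, what remains of the first rule is mainly a question of target population, with the reservation that the baseline answer is itself given after schools know their arm.

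**What to change.** 1. Define the primary analysis set as all consenting students, in the arm to which their school was randomised, including those in psychotherapy.
2. Use every available PSS-10 value, baseline included, in a multilevel model or with multilevel multiple imputation. Let this replace the deletion rule in Retention {18b}, and align Missing data {20c} with it.
3. Keep the psychotherapy exclusion only as a sensitivity analysis, defined by the baseline answer and never by a later one.

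The cost is revised wording for the analysis set and one additional analysis. There are two downsides. Students already in treatment may slightly dilute the effect, and students with no follow-up add little precision when only their baseline is available. The change does not address any difference between arms in consent itself, which students give on the first page of a survey that follows randomisation.

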### Who will take informed consent? {26a}

For the trial, the informed consent of the respective schools’ head teachers is required, as well as the informed consent of a legal guardian and of the students. If schools express an interest in participating, a meeting will be organised in order to provide detailed information about the study. In the case of participation, the legal guardians of students in the participating grades/classes will be given detailed written information sheets and will be able to watch an online presentation, in which the study is orally explained. The students will receive posters with information. If students wish to participate, they will provide their written consent by clicking on “Yes, I do want to participate in the study” on the first page of the online survey.

### Additional consent provisions for collection and use of participant data and biological specimens {26b}

Not applicable. No biological specimens will be collected.

## Interventions

### Explanation for the choice of comparators {6b}

In prevention research, a comparison of an intervention group and a waiting list control group is common for ethical reasons [42]. In order to test the effectiveness of a universal prevention program, comparing these two groups seems reasonable and cost-effective. As we will be working with adolescents, we will ensure that every school in the waiting list control group will be offered the intervention directly after the final assessment (6-month follow-up), enabling all adolescents to eventually benefit from the programme.

### Intervention description {11a}

#### Intervention

*LessStress* - A universal prevention programme in school - was designed by a team of psychologists, scientists, and psychiatrists with a focus on preventing mental health problems in adolescents. The intervention consists of two parts: a 90-min interactive lesson in class, which is combined with a booklet, called *Stresserwizzer*. The 90-min lesson will be presented to the class by school staff, who will receive corresponding training in advance. The lesson is divided into three main topics of emotion regulation, mindfulness, and self-compassion. Students will be given background information (what are emotions, how do we know what we are feeling, how are our emotions linked to our body, thoughts and behaviour, how can we change emotions/what is mindfulness, how can I be mindful in my daily life/what is self-compassion, how can I be more compassionate) and exercises on each topic. All exercises can be done alone or in small groups. Each student receives a workbook that contains information conveyed in the lesson as well as the exercises themselves. An important topic discussed with students is their ability to use skills. The idea is to have the class discuss what they have been doing to maintain their health so far or what they usually do to improve their mood. In a next step, students should think about other things/strategies they could try out in the future. It is important to connect the things they have learned theoretically about controlling their own emotions with things they can apply and integrate into their daily lives. The open discussion in class should also be beneficial to students who have used fewer skills so far and are less integrated in terms of social life. By hearing others talk about their experiences, they might want to try new things. In a next step, mindfulness is discussed, and the students experience different types of meditation. They are asked to think of situations in their daily lives when they have already been mindful and to think of situations to be more mindful in. Following the topic of mindfulness, self-compassion and also the connection to the self-critical inner voice will be discussed (what is the difference between self-pity and self-compassion, do I know this critical inner voice in me, what does it do, how can I deal differently with defeats or mistakes in the future). The main basis of this intervention is dialectical behavioural therapy for adolescents (DBT-A [62–64]) as well as studies evaluating the effectiveness of mindfulness for stress reduction [30, 31]. The aim of this lesson is to (1) convey skills that can help students protect themselves from stress and its consequences using a rather open approach and (2) address the topic of stress in teenagers and stress in school. The “rather open approach” here refers to experiential education content: For the most part, the students need to work out the content for themselves and not be silent listeners (e.g. group work, small-group or the whole-class discussions, and so on). Actively involving the students in the process of the lesson should ultimately enable the content to be better linked and remembered. Particularly regarding the topics emotion regulation and self-compassion, we want the students to experience different strategies and find out what works best for them individually. For most students, it is very likely that *LessStress* will be the first time they have done a mindfulness exercise, as mindfulness is not yet very common in German schools. In addition, students are given a 40-page booklet that contains useful information about stress in general and specifically about stress at school, along with helpful advice about what to do when feeling overwhelmed [65, 66]. This booklet has a modern design targeted at arousing adolescents’ interest. Students should read the booklet by themselves, and teachers should refer to the booklet from time to time to bring it back to the students’ minds. The posters of the study, which serve to provide information for the students about the purpose and process of the study, also fulfil another task: Through their presence in the classroom, they provide a “daily reminder” and better transfer of the content from the lesson and booklet into students’ daily lives.

### Criteria for discontinuing or modifying allocated interventions {11b}

All participating schools will be supported by our study team during the implementation of the programme. Experience from other studies conducted in schools has shown that weekly contact by email and telephone is a good way to stay in touch and to clarify questions quickly. Through regular exchange and contact with the teachers carrying out the programme, difficulties should be detected and corrected in advance in order to improve adherence.

### Strategies to improve adherence to interventions {11c}

#### Adherence

Each participating school (and especially the staff) will receive online training before administering the programme. This training will focus on the implementation of the PowerPoint presentation guiding the lesson and will also refer to the booklet. Furthermore, two to three small role-plays on crises will be carried out to prepare the teachers for all eventualities, such as students reporting non-suicidal self-harm to the teachers or students becoming highly stressed (e.g. starting to cry, needing to leave the room). To check adherence during the intervention, we will ask the school staff to fill out an online survey measuring their adherence to the given instructions. Questions will be asked about the presentation itself, how well students have understood the topics, whether everything was discussed, what questions remained, how easy it was for the teachers, and how well they think the class liked it.

In a next step, this information should be used in order to improve the presentation if necessary.

### Relevant concomitant care permitted or prohibited during the trial {11d}

During the implementation phase of *LessStress*, no other prevention programme should be carried out in the participating classes at the schools during the relevant period. Normal teaching and the general curriculum are, of course, allowed.

### Provisions for post-trial care {30}

One positive side effect of this trial is the networking between schools and clinicians. We aim to reduce stigmatisation and encourage communication. If any student requires healthcare during or after the study, the Department of Child and Adolescent Psychiatry of Rostock will offer appointments. We are confident that by being present and talking to the schools and students, we can lower the threshold, enabling students to seek help more frequently and faster.

### Outcomes {12}

#### Primary outcome

Differences between the two groups (IG and WL) regarding self-perceived stress measured with the *Perceived Stress Scale* (PSS-10) [46, 47, 67] at 3- and 6-month follow-ups.Scores on the PSS-10 range from 0 = *no stress at all* to 40 = *maximum stress*. We assume a significant reduction in the intervention group.

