### Objectives

In order to find out whether the universal prevention programme *LessStress* has a significant impact on students’ subjective experience of stress, the intervention group (IG) will be compared with a waiting list control group (WL) in terms of scores on the *Perceived Stress Scale 10* (PSS-10) [46, 47].

We expect that students who take part in the universal prevention programme *LessStress* will significantly benefit, as measured by the primary and secondary outcomes. Given the preventive nature of the programme, we expect to find a decrease in self-perceived stress and fewer mental health problems in the IG after 6 months, which will be assessed with the secondary outcomes.

To test the efficacy, we will collect data using self-administrated questionnaires, which will be implemented within an online survey. The questionnaires are standard instruments in the field of psychology and show good psychometrics properties. Questionnaires remain the means of choice to assess personal states and feelings.

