### Sample size {14}

To analyse cluster-randomised trials, specific constraints must be followed, as individuals within a cluster are assumed to be more similar compared to individuals from different clusters. In order to detect significant effects, the sample size of the trial must be adjusted. This so-called clustering effect (1 + (*m*-1)×*p* [*m* = average number of subjects per cluster; *p* = intraclass correlation coefficient (ICC)]) resulted in an estimated *N* = 1795. For *m*, we assumed an average of 80 within an entire grade as the average class size in Germany varies nationwide (21.2–30.4 students per class), and the ICC was estimated quite conservatively at approximately 0.05 [70] on the basis of the primary outcome. Hence, a clustering effect of 4.95 was determined. Assuming a small effect size (Cohens *d* = 0.2) in universal prevention based on previous studies [71], with a significance level alpha = 0.05 and a power = 0.9, g*power suggests a total of *N* = 306 [72]. Considering the clustering effect, we have to multiply this by 4.95, reaching an overall *N* = 1515. Assuming a dropout rate of 25% due to moving out of the area, sickness, or other reasons, we must add another 379, leading to the final *N* = 1894.

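### The primary endpoint is stress at 6 months in the trial design section but at both 3 and 6 months in the outcomes section, and the two must be made to agree

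*Protocol article*

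**What the plan says.** Two sections of the protocol article define the primary endpoint, and they differ.

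- Trial design {8}: the trial has "a primary endpoint of self-perceived stress after 6 months". The same section lists the two follow-ups as separate assessments: "T2 = 3-month follow-up, and T3 = 6-month follow-up".
- Outcomes {12}, Primary outcome: the endpoint is the difference between intervention and waiting list on the scale, given as "PSS-10) [46, 47, 67] at 3- and 6-month follow-ups".

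The other sections that could settle it do not:

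- Primary objectives names the scale and the expected direction, but no time point.
- Sample size {14} works "with a significance level alpha = 0.05 and a power = 0.9" and a single standardised effect of 0.2. It attaches neither to a time point and does not state whether the test is one- or two-sided.
- Statistical methods {20a} compares the groups on their change, by multilevel model or mixed ANOVA depending on the ICC. It does not say up to which assessment the change runs or which model term decides.

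**The concern.** The primary endpoint decides whether the trial succeeded, and here the answer can depend on which section is read. Suppose the groups differ at 3 months but not at 6. The article does not predict this, but it is a possible result. Under Trial design {8} the trial is negative. Under Outcomes {12} it could be reported as positive. With both definitions published, the choice could be made after the results are known. This matters more because the trial is unblinded and the outcome is self-reported.

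The definition also determines which data are critical. Under the retention rules a student is left out of the analysis only if more than one follow-up is missing, so a student with a 3-month but no 6-month score stays in. Whether that student lacks the whole primary measurement or part of it depends on which section holds.

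**Working it through.** **1. The plan's own figure.** Inputs from Sample size {14}: m = 80, ICC = 0.05, d = 0.2, alpha = 0.05, power = 0.90, base N = 306, dropout 25%.

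- Design effect: 1 + (80 − 1) × 0.05 = 4.95, as stated.
- 306 × 4.95 = 1514.7, rounded to 1515, as stated.
- 1515 × 0.25 = 378.75, rounded to 379; 1515 + 379 = 1894, as stated.

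The base of 306 does not follow from a two-group comparison of means with these inputs, which needs 1052 in total two-sided or 858 one-sided (normal approximation). That is a separate matter. Here it means only that the calculation is weak evidence of which endpoint was intended. The steps below take the stated power of 0.90 at face value.

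**2. Assumptions the article does not supply.** Two-sided testing, and the correlation r between the 3-month and 6-month test statistics, shown over a range.

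**3. Reading A: either time point suffices, each tested at 0.05.**
Type I error = 1 − P(|Z₁| ≤ 1.96 and |Z₂| ≤ 1.96), with Z₁, Z₂ bivariate normal with correlation r. For r = 0 this is 1 − 0.95² = 0.0975. The upper bound for any r is 0.05 + 0.05 = 0.10.

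| r | Type I error |
|---|---|
| 0 | 0.0975 |
| 0.3 | 0.095 |
| 0.5 | 0.091 |
| 0.8 | 0.078 |
| 0.9 | 0.070 |

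**4. Reading B: both time points required, each at 0.05.**
Type I error does not exceed 0.05. If each test has power 0.90, joint power = Φ₂(1.2816, 1.2816; r), the bivariate normal distribution function.

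| r | Joint power |
|---|---|
| 0.3 | 0.822 |
| 0.5 | 0.832 |
| 0.7 | 0.847 |
| 0.8 | 0.856 |

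**5. Reading C: either suffices, alpha split at 0.025 each.**
Type I error is 0.049 at r = 0 and 0.043 at r = 0.7. At unchanged N, a test with power 0.90 at 0.05 has power Φ(1.960 + 1.2816 − 2.2414) = Φ(1.000) = 0.84 at 0.025. Restoring 0.90 per time point takes the number per arm before clustering from 526 to 621, a factor of 621 / 526 = 1.18. Applied to the stated total, 1894 × 1.1806 ≈ 2236.

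**6. Reading D: one joint group-by-time test at 0.05.** There is one test, so alpha is not inflated. It answers a different question from a 6-month contrast.

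**7. Reading E: 6 months only, as in Trial design {8}.** There is one test, type I error is 0.05, and the stated alpha needs no adjustment.

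**The case against.** A reader might infer that the plan gives the trial two unadjusted chances of success. The article does not support that. Nowhere does it plan a separate test at each follow-up or say that one significant result is enough. Outcomes {12} joins the time points with an 'and', and the mixed ANOVA or multilevel model in Statistical methods {20a} could carry both follow-ups in one joint test. The inflated error rate belongs to the either-or reading alone and rests on assumed sidedness and correlation. This part of the objection stands.

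Success rules and multiplicity handling may also sit in an analysis plan that is not shown, so their absence from an article is not held against it. That stands too, but it does not remove the point. An analysis plan implements the protocol's primary endpoint, and here there are two: following one section contradicts the other.

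It is also tempting to settle the matter in favour of 6 months from the Objectives section, which expects "decrease in self-perceived stress and fewer mental health problems in the IG after 6 months". That sentence goes on to tie the assessment to the secondary outcomes, so it cannot decide what is primary. Nor does Trial design {8} fix how the 6-month endpoint is tested: it gives the time point only, alpha comes from Sample size {14}, and no section states two-sided testing.

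Finally, 6 months alone is not the only defensible choice. Outcomes {12} is the formal definition of the outcome, and keeping both time points under a stated rule would also resolve the conflict.

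**Conclusion.** The inconsistency is real. The primary endpoint has one time point in Trial design {8} and two in Outcomes {12}, and nothing else in the article reconciles them. It needs correcting because the readings can lead to different conclusions from the same data.

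The size depends on the reading:

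- Either time point sufficient: type I error about 0.07 to 0.10 instead of 0.05.
- Both required: alpha not inflated, power about 0.82 to 0.86 instead of 0.90 for correlations of 0.3 to 0.8.
- One joint test, or 6 months alone: alpha not inflated.

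These figures assume two-sided tests, correlations that the article does not give, and the stated power at each time point. Confidence is high that the definitions conflict. That two unadjusted tests are planned is not established.

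**What to change.** Make Trial design {8} and Outcomes {12} agree before outcome data are seen.

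The simplest way is to name the between-group difference in PSS-10 at T3 (6 months) as the sole primary endpoint in both sections, tested at the stated alpha of 0.05 with the sidedness written down, and to list the 3-month difference as secondary. The stated alpha then needs no division.

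If the sponsor prefers to keep both time points primary, Trial design {8} should say so, and the success rule should be fixed as one joint test, both required, or a split alpha. The stated power or sample size should be restated where the rule changes it: about 0.82 to 0.86 joint power if both are required, or about 18% more students to keep 0.90 per time point if alpha is split.

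The first option costs a sentence or two and no extra data. By the article's own rules on amendments, any change also needs a formal amendment to the ethics committee and the education ministry. The registry record was not available here and should be checked for the same discrepancy.
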